#### Exploratory outcome

The exploratory outcomes will include overall survival (OS) and progression-free survival (PFS). PFS and OS are defined from start of treatment until recurrence or date of death.

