### Study population

The patients included in the study are those with a diagnosis of advanced primary lung cancer and prescribed combination immunotherapy as first-line treatment. The inclusion and exclusion criteria for this study are listed in Table 1.

**Table 1 Tab1:** The inclusion and exclusion criteria for this study

Inclusion criteria	Exclusion criteria
✓ Pathologically confirmed advanced or stage IV primary lung cancer who had no surgical indicators.	× Age < 18 years old at the time of informed consent.
✓ Scheduled to receive combination immunotherapy as the first-line treatment.	× Cognitive impairment or inability to understand the research content.

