### Data analysis

Participants who meet the withdrawal criteria for the study will not be included in the final analysis. For the study results, descriptive analysis will be undertaken by using mean ± SD or median with interquartile range (IQR) for continuous variables, and absolute number (n) and proportion (%) for categorical variables. First, we will use descriptive statistics to describe the severity and time trend of symptom burden and functional interference in patients treated with combination immunotherapy. Symptom trajectories will be depicted with line graphs describing the severity score of patients reporting symptoms from pre-treatment to complete the whole treatment course for 1 month. Furthermore, the association between symptom and clinical outcomes will be examined. Specifically, the symptoms will be categorized based on the severity, and the difference in clinical outcomes (including incidence rate of grade 3–4 immunotoxicity, the completion rate of six cycles of immunotherapy, the timeliness of treatment, complication rate, unplanned clinic rate, OS and PFS) will be assessed. We will use R v.4.2.0 to perform the statistical analysis, and differences will be considered statistically significant if the two-tailed *p*-values are < 0.05.

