## List of Abbreviations

CTCAE: Common Terminology Criteria for Adverse Events
ePROs: Electronic patient-reported outcomes
irAEs: Immune-related adverse events
ICIs: Immune checkpoint inhibitors
MDASI-LC: MD Anderson Symptom Inventory–Lung Cancer module
OS: Overall survival
PFS: Progression-free survival
PRO: Patient-reported outcome
PROM: patient-reported outcomes measures
SOP: Standard operating procedure

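### OS and PFS are given one shared definition that ends at recurrence or death, so at least one of them is wrongly defined on any reading

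*Protocol article*

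**What the plan says.** Under Exploratory outcome, the protocol article first names two endpoints: "The exploratory outcomes will include overall survival (OS) and progression-free survival (PFS"). It then defines both together: "PFS and OS are defined from start of treatment until recurrence or date of death". No *respectively* appears, and neither endpoint is defined anywhere else. The Background, Data analysis, Discussion and abbreviation list only name them; the last gives just the expansion "PFS: Progression-free survival".

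Table 1 (Study population) describes who is enrolled: "Pathologically confirmed advanced or stage IV primary lung cancer who had no surgical indicators", and "Scheduled to receive combination immunotherapy as the first-line treatment".

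The Data analysis section groups symptoms by severity and compares clinical outcomes between the groups. OS and PFS close that list as two separate items: "the timeliness of treatment, complication rate, unplanned clinic rate, OS and PFS) will be assessed". The Discussion repeats the list.

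**The concern.** OS and PFS differ only in which events end the clock. Giving them the same events removes the difference. A sentence that assigns one start and one pair of end events to both endpoints makes OS stop at a non-fatal event, which is not overall survival.

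The non-fatal event is also misnamed. Recurrence means that disease returns after it has been cleared. Patients starting first-line treatment for advanced or stage IV disease have active disease at the time origin, so the event to expect is progression. The article never names progression as an event; the word occurs only in the name of the endpoint.

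What is at stake is the link between symptom burden and survival, one of the associations the study sets out to examine. If the sentence is followed as written, the OS and PFS comparisons are one analysis reported twice, and a reader could mistake that for agreement between two endpoints.

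**Working it through.** The article states no event count, median, power or alpha for OS or PFS, so there is no figure to reproduce. The check is a comparison of definitions.

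**Notation.** Measure all times from the start of treatment. Let D be time to death from any cause, P time to first documented progression, and R time to recurrence.

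**Usual definitions.** OS = D. PFS = min(P, D).

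**As written.** OS = min(R, D) and PFS = min(R, D).

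Two things follow without any assumption about event rates:

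1. OS and PFS are equal for every patient. Every curve, hazard ratio and p-value comparing symptom groups is therefore the same for both.
2. Since min(R, D) ≤ D, OS as written can never exceed true survival time, and it falls short in every patient who has the non-fatal event before death.

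**Can a kinder reading rescue the sentence?** Two choices are open: whether *respectively* is implied, and whether *recurrence* stands for progression. All four combinations are:

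| Reading | OS becomes | PFS becomes | What is wrong |
|---|---|---|---|
| Shared events, recurrence as written | min(R, D) | min(R, D) | OS counts a non-fatal event; PFS does not count progression |
| Shared events, recurrence means progression | min(P, D) | min(P, D) | OS counts a non-fatal event; PFS is right |
| Respectively, recurrence as written | D | R | OS is right; PFS omits progression and death |
| Respectively, recurrence means progression | D | P | OS is right; PFS omits death, so it is time to progression |

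No row gets both endpoints right. The readings that repair OS break PFS, and the one that repairs PFS leaves OS wrong.

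**Does anything else depend on the definition?** The Sample size calculation rests on a symptom-score comparison (1.6 ± 1.1 against 1.0 ± 0.7, 30% with adverse events, 90% power, two-sided 5%, 20% dropout, 168 patients). The primary outcome is symptom burden. Neither uses OS or PFS.

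**The case against.** The best case for the sponsor is that the meaning is obvious. Both endpoints are spelled out by their standard names and listed separately, so a compressed sentence meaning PFS to recurrence and OS to death is a plausible intent. Both are exploratory, the study is observational, and no sample size or error rate hangs on them. This stands in part. The identity of OS and PFS holds only for the shared-events reading, and the stakes are modest. It does not clear the sentence, because under the charitable reading PFS loses death as an event.

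It could also be said that a journal article leaves endpoint detail to the full protocol or analysis plan. That is true of censoring rules and response criteria, and their absence is not criticised here. The point concerns a definition the article does state, and states wrongly.

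A reader might go further than the document allows in three ways:

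- **A number of surplus OS events.** The article gives no survival or progression medians, cycle length or time at which OS and PFS are evaluated, so any count would rest wholly on outside assumptions. It would also sit badly with the naming problem. If recurrence seldom applies to these patients, an OS that counts it collects few extra events. If it is read as progression, the extra events may be many, but PFS is then correctly defined. The two faults cannot both act at full size.
- **Patients can never become disease-free.** The article does not say so. The abstract includes locally advanced disease, the Background mentions combination with radiation, and complete response is not discussed. What Table 1 supports is that disease is active at the time origin.
- **Death dates after a recurrence will be lost.** The case report form is not shown, so this is something to verify and not a finding.

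**Conclusion.** The point holds: the single sentence misdefines at least one of the two endpoints on each of the four readings, and read literally it makes them the same variable. This rests only on the usual meanings of OS and PFS and on the article's own text. *Recurrence* is the wrong event name for the population in Table 1.

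The consequence is limited to the exploratory associations of symptom severity with OS and PFS. The primary outcome, the sample size and the other secondary outcomes are untouched. No numerical size for the error can be derived from the document. The wording should be corrected before those associations are analysed, but it does not threaten the study's main objective.

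**What to change.** Keep the stated time origin, with which nothing is wrong, and replace the sentence with two:

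- OS: time from start of treatment to death from any cause.
- PFS: time from start of treatment to first documented disease progression or death from any cause, whichever comes first.

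This removes *recurrence* in favour of *progression*. Confirm that the case report form holds the date of progression and the date of death as separate fields, so that a death after progression is still captured for OS.

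The cost is two sentences and a check of the form. Recruitment began in July 2022 across 14 hospitals; if the form turns out to hold only one combined date, the missing date would have to be retrieved for patients already followed, and telephone follow-up is already planned for data that do not come from the medical record. No change to the sample size, the schedule or the primary analysis is needed.

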### Data collection, management, and monitoring

The collected data will include demographics, clinical characteristics before treatment, PROs, and clinical outcomes as mentioned above. PRO data will be collected at baseline (before treatment), treatment onset, and once a week (± 2 days) after receiving treatment until admission to the hospital for the next cycle of treatment. Furthermore, the previous step of PRO data collection will be repeated until six cycles of immunotherapy have completed for 1 month. The study schedule of this study is shown in Fig. 2.

**Fig. 2 Fig2:**
[figure not shown]
Study schedule of enrolment, data collection and timeline

An electronic questionnaire is the primary form of PROs data collection, which will be sent to patients through a link or quick response code and will be completed by the patients on their own unless they ask for assistance. In addition, demographics and clinical characteristics before treatment will be obtained from the electronic medical record system, and other data will be obtained through telephone follow-up.

The project team is composed of multiple functional roles, including a data manager, a data monitor, and data quality control staff. The data manager is responsible for organizing the form design, database establishment, standard operating procedure (SOP) production, researcher training, and daily management. REDCap, a web-based software application for data storage and management, will be utilized for case report form design, database establishment, and data management in our study. Regarding the data monitor and quality control staff, the data monitor will take charge of inspecting the entered data once every 3 months, and the quality control staff will be responsible for the quality of the data and the progress of the study.

### Quality control

The present study will be implemented by and receive guidance and supervision from a multidisciplinary team comprising the principal investigator, subcenter principal, clinicians, clinical research methodologists, statisticians, research assistants, data managers, data monitors, and data quality control staff. A SOP will be proposed as an important reference to guarantee the quality of entered data, and all participants involved in the study are bound to receive SOP training prior to starting the recruitment of patients. As for subcenters, investigators will receive regular online guidance and telephone supervision, and on-site monitoring from the principal investigator to control the quality of data entry. When entering the data, the REDCap system can immediately execute automatic logical verification to correct the faults in this process. In addition, there will be regular and non-scheduled data checking during the patient recruitment process, and all data will receive a final verification for completeness and accuracy after data entry.

### Data confidentiality

To protect data privacy, participants involved in the study will get a unique study ID (consisting of two sets of numbers) for personal identifying information that is not irrelevant to the assessment. All data (including all personal data) will be stored in the REDCap of Sichuan Cancer Hospital, and all investigators will have access to them.

### Data analysis

Participants who meet the withdrawal criteria for the study will not be included in the final analysis. For the study results, descriptive analysis will be undertaken by using mean ± SD or median with interquartile range (IQR) for continuous variables, and absolute number (n) and proportion (%) for categorical variables. First, we will use descriptive statistics to describe the severity and time trend of symptom burden and functional interference in patients treated with combination immunotherapy. Symptom trajectories will be depicted with line graphs describing the severity score of patients reporting symptoms from pre-treatment to complete the whole treatment course for 1 month. Furthermore, the association between symptom and clinical outcomes will be examined. Specifically, the symptoms will be categorized based on the severity, and the difference in clinical outcomes (including incidence rate of grade 3–4 immunotoxicity, the completion rate of six cycles of immunotherapy, the timeliness of treatment, complication rate, unplanned clinic rate, OS and PFS) will be assessed. We will use R v.4.2.0 to perform the statistical analysis, and differences will be considered statistically significant if the two-tailed *p*-values are < 0.05.

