### Withdrawal criteria

Participants will be withdrawn from the study, and no further data will be collected if they meet the criteria, as shown in Table 2.

**Table 2 Tab2:** The withdrawal criteria for the study

Withdrawal criteria
1. Cancelling planned immunotherapy before the treatment.
2. Patients who break the study protocol (deliberately offering inaccurate PRO data).
3. Patients who demand an immediate withdraw from the research.
4. Severe complications interfering with PRO data collection.
5. Other conditions that require withdrawal as assessed by the investigator.

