### Outcome measures

#### Primary outcome

The primary outcome of this study is the symptom burden in patients with lung cancer during the first-line combination immunotherapy course. It will be assessed using the MDASI-LC and symptomatic irAEs scale directly from patient self-reports. MDASI-LC [17], the lung cancer-specific PRO measurement, will be translated into simplified Chinese to collect longitudinal symptom data once before treatment (typically within 3 days before treatment) and weekly throughout the treatment and till 1 month after treatment completion. It comprises 16 symptoms (pain, fatigue, nausea, disturbed sleep, distress, short breath, remember things, lack of appetite, drowsy, dry mouth, sad, vomiting, numbness, cough, constipation, and sore throat) and six functional items (activity, mood, work, relations, walking, and enjoy life). Each item uses a 0-10-point scale, with 0 representing “symptom has not been present or no functional impairment” and 10 representing “the most severe symptoms or functional impairment”. In addition, the symptomatic irAE scale is a subgroup of symptomatic irAE items from the Patient Reported Outcomes version of the Common Terminology Criteria for Adverse Events library [18, 19], which provides a valid and reliable assessment of symptomatic toxic effects from the patient’s perspective, and is encouraged for use in oncology trials to enhance the accuracy of adverse event reporting [19]. The scale consisting of 15 items (bellyache, diarrhea, bloated pain, night sweats, headache, rash, chills and fever, pruritus, pectoralgia, hemoptysis, abdominal, early satiety, taste change, smell change, and palpitation) will be translated into Chinese to collect the severity score of irAEs. Like the MDASI-LC, it also uses a 0–10 scale, where 0 represents “symptom has not been present or no functional impairment” and 10 represents “the most severe symptoms or functional impairment”.

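### Primary symptom trajectory: the plotted population is ambiguous and withdrawn patients are left out, so the raw weekly line may misstate the burden

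*Protocol article*

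**What the plan says.** The Primary outcome section states: "The primary outcome of this study is the symptom burden in patients with lung cancer during the first-line combination immunotherapy course". Each item is scored 0 to 10, "with 0 representing “symptom has not been present or no functional impairment", so 0 is a valid observation and not a missing one.

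The Data analysis section fixes how the trend is summarised. It says "we will use descriptive statistics to describe the severity and time trend of symptom burden and functional interference in patients treated with combination immunotherapy", using "mean ± SD or median with interquartile range (IQR) for continuous variables". The next sentence defines the figure: "Symptom trajectories will be depicted with line graphs describing the severity score of patients reporting symptoms". No longitudinal model is named, and nothing says whether zeros enter the line.

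The same section opens with an exclusion: "Participants who meet the withdrawal criteria for the study will not be included in the final analysis". Table 2, under Withdrawal criteria, includes "Severe complications interfering with PRO data collection" among the grounds. Under Study setting, each patient is followed until one month after the last immunotherapy cycle.

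**The concern.** Two consecutive sentences name two populations for the same result: all treated patients, then patients who report symptoms. If the second is taken at its word, someone who scores 0 for a symptom in a given week is not reporting it and is not in that week's average. The line then mixes how many patients have the symptom with how badly those patients have it.

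This matters most for symptoms that appear during treatment. The 15 immune-related items were added to capture such symptoms. When many patients newly develop a mild symptom, they enter the average at low values and pull it down.

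The second route does not depend on how that phrase is read. Removing everyone who meets a withdrawal criterion also removes the scores they gave beforehand, and one criterion is tied to severe illness. Patients whose treatment ends early stop contributing to later weeks. Simple weekly means correct for neither. The trajectory is the study's main result and is offered as a reference for clinicians, so its level and direction both matter.

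**Working it through.** **The plan's own figure.** The only design figure is the sample size of 168, and it reproduces. With a 30:70 split, means 1.6 and 1.0, SDs 1.1 and 0.7, two-sided 5% and 90% power:

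N = (1.960 + 1.282)² × (1.1²/0.3 + 0.7²/0.7) / 0.6² = 138.2.

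Rounded up by group this is 42 + 98 = 140, and 140 × 1.2 = 168. The present point does not depend on it.

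**Denominator, literal reading.** For any item and week,

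all-patient mean = proportion scoring above 0 × mean among those scoring above 0.

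The documents give no symptom prevalence, so the prevalences and scores below are assumed.

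| Illustration | Week | Pattern | All-patient mean | Reporters-only mean |
|---|---|---|---|---|
| 1 | early | 20% at 3.0 | 0.20 × 3.0 = 0.6 | 3.0 |
| 1 | late | 50% at 2.0 | 0.50 × 2.0 = 1.0 | 2.0 |
| 2 | early | 20% at 5.0 | 0.20 × 5.0 = 1.0 | 5.0 |
| 2 | late | same 20% at 5.5, a further 30% at 2.0 | 1.1 + 0.6 = 1.7 | 1.7/0.5 = 3.4 |

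In illustration 1 the burden rises by 67% while the line falls by 33%. In illustration 2 no patient improves, yet the line still falls.

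**When the reversal happens.** The reporters-only mean changes by (ratio of all-patient means) / (ratio of prevalences). It falls while burden rises only if prevalence grows by a larger factor than the all-patient mean. Take a rise in the all-patient mean from 1.0 to 1.6, borrowing the two preliminary group means purely as a scale:

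| Prevalence grows by | Reporters-only mean changes by |
|---|---|
| 1.2 | 1.6/1.2 = 1.33 |
| 1.6 | 1.00 |
| 2.0 | 0.80 |
| 2.5 | 0.64 |

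**Denominator, alternative reading.** If the phrase means all who complete the questionnaire, zeros stay in, the plotted quantity is the all-patient mean, and the reversal cannot arise.

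**Exclusion of withdrawn patients.** If a fraction w is removed, the mean in those retained falls short of the full mean by w × (mean of removed − mean of retained). For a sense of scale, use the preliminary scores. The mean over all patients is 0.3 × 1.6 + 0.7 × 1.0 = 1.18. Suppose the whole 20% dropout allowance came from the adverse-event group. Those retained would then average (0.1 × 1.6 + 0.7 × 1.0)/0.8 = 1.075, a shortfall of 0.105 points or about 9%. If removal were unrelated to burden, the shortfall would be 0. These are assumed cases, not limits: the plan gives no reasons for dropout, and patients with severe complications could score above 1.6.

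**The case against.** The strongest reply is that, in a study of self-reported outcomes, patients who report symptoms may simply be those who complete the self-report. The preceding sentence covers all treated patients and 0 is a defined score. The low preliminary means (1.0 and 1.6 on a 0–10 scale) suggest, if anything, that zeros were counted there, although how that score was formed is not stated. This stands. A reader might infer that the plan discards zeros, but no sentence says so. What is established is that the wording permits it.

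A reader might also infer that a reversal would be common. The documents do not show that. The prevalences above are assumed, and with a 1.2-fold growth in prevalence the reporters-only line still rises.

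A third tempting reading is that the late part of the curve describes only patients who stayed well. The exclusion rule works differently: those who meet a withdrawal criterion leave the whole curve, baseline included. Early stoppers do thin out the later weeks, but the documents do not say that the sickest leave first.

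Finally, descriptive plots suit a descriptive aim, and model details commonly sit in an analysis plan that is not shown. That disposes of any demand for a full modelling package. It does not answer the rest, because the article itself states the summary method, the plotted population and the exclusion.

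**Conclusion.** The point holds as an ambiguity in the primary display together with a stated exclusion that can bias it. It is a change the sponsor should make, but it does not show that the trajectory will be wrong.

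On the literal reading the line can move opposite to the burden (+67% against −33% in the first illustration). On the other reading that error is absent. The exclusion and early stopping apply on either reading, and they understate burden only if the patients lost carry more of it than those kept. The severe-complications criterion makes that plausible for withdrawals. The reasons for early stopping are not given. On the scale of the preliminary scores, the assumed cases for exclusion run from no effect to about 0.1 points.

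**What to change.** 1. In Data analysis, state that each weekly point covers all assessed treated patients with zeros kept. Show the percentage scoring above 0 in a separate panel, and print the number contributing each week. Name the mean as the plotted statistic: with zeros kept, a median is 0 whenever fewer than half of patients score above 0.
2. Amend the exclusion sentence so that scores collected before withdrawal stay in the analysis, where consent allows and the data were not deliberately inaccurate. Patients who cancelled before treatment fall outside a treated population in any case.
3. Beside the raw plot, estimate the trend with a repeated-measures mixed model (week as categorical or spline, patient random effects) and give 95% confidence intervals. It uses the available scores of patients who leave early and allows for correlation within patients. A sensitivity analysis for informative dropout is optional.

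The cost is revised wording and modest extra R programming, with no new data. One limitation remains: a linear mixed model only approximates a bounded score with many zeros, which is a reason to keep the raw plot and the percentage panel next to it.

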**Methods:**

We will prospectively recruit 168 eligible patients from 14 hospitals in China. Eligible patients will be aged ≥ 18 years, pathologically diagnosed with locally advanced or stage IV primary lung cancer without surgical indications, and agreed to receive immunotherapy in combination with other therapies. The primary outcome of this study is the symptom burden of patients during the immunotherapy course. Longitudinal symptom data will be collected using the MD Anderson Symptom Inventory–Lung Cancer module (MDASI-LC) and the symptomatic irAEs scale at baseline (once before treatment) and weekly after treatment, until 1 month after the last treatment cycle has been completed. The trajectory of symptom burden following combination immunotherapy will be depicted, and by linking it to clinical outcomes (the secondary outcome and exploratory outcome of this study), the consequence of symptom burden in patients with advanced lung cancer receiving combination immunotherapy will be examined further.

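### Symptom severity is to be related to outcomes that arise while it is still being reported, with no rule that the reports come before the outcome

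*Protocol article*

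**What the plan says.** The Data analysis section of the protocol article states that "the symptoms will be categorized based on the severity, and the difference in clinical outcomes" will be assessed. It lists seven outcomes: grade 3–4 immunotoxicity, completion of six cycles, timeliness, complications, unplanned visits, OS and PFS, each at a two-sided 5% level. It gives no reporting window, summary measure or cut-off for the severity category.

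Other sections indicate which symptom burden is meant:

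- Abstract, Methods: "The trajectory of symptom burden following combination immunotherapy will be depicted, and by linking it to clinical outcomes", the study will examine the consequence of that burden.
- Primary outcome: "The primary outcome of this study is the symptom burden in patients with lung cancer during the first-line combination immunotherapy course". Reports are collected "weekly throughout the treatment and till 1 month after treatment completion".
- Data collection: "PRO data will be collected at baseline (before treatment), treatment onset, and once a week (± 2 days) after receiving treatment", and this "will be repeated until six cycles of immunotherapy have completed for 1 month".
- Exploratory outcome: "PFS and OS are defined from start of treatment until recurrence or date of death".

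The symptom instruments include 15 patient-reported irAE items (Primary outcome). Immunotoxicity is graded by CTCAE v5 and classified by organ system (Secondary outcome).

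**The concern.** The grouping variable is built from data recorded after the outcome clock has started, and both the amount and the timing of those data can depend on the outcome. Two distinct problems follow.

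**(a) Length of observation.** A patient who stops, progresses or dies early files fewer reports and has fewer chances to record a severe one. Under some severity rules this alone makes severe symptoms look protective.

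**(b) Reversed order.** A report filed after an irAE or an unplanned visit can place the patient in the severe group, which is then said to be associated with that same event. Some irAE items, such as rash and diarrhea, describe manifestations that may also be graded as immunotoxicity, so the two sides of the comparison partly overlap.

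At stake is the study's second aim, linking symptom burden to clinical outcomes. The descriptive trajectories of the primary outcome are not affected.

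**Working it through.** **Step 1. The plan's own figure.** The only computed figure is the sample size, which is not in dispute and serves here only to set the number of evaluable patients. With a 30:70 split, SDs of 1.1 and 0.7, a difference of 1.6 − 1.0 = 0.6, two-sided 5% and 90% power:

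N = (1.960 + 1.282)² × (1.1²/0.30 + 0.7²/0.70) / 0.6² = 138.2.

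Allowing for 20% dropout gives 138.2 × 1.2 = 166, or 138.2 / 0.8 = 173. The stated 168 lies between them. Evaluable patients: 168 × 0.8 = 134.

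**Step 2. Six-cycle completion under no true association, *ever severe* rule.** The documents give none of the following, so they are assumptions: 3-week cycles; 70% complete six cycles; the rest stop after k = 1 to 5 cycles, equally often; reports run to 4 weeks after the last cycle; the weekly chance of a first severe report is 5%, independent of completion.

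- Completers, 22 weeks: P(ever severe) = 1 − 0.95²² = 0.676.
- Non-completers, 3k + 4 = 7, 10, 13, 16, 19 weeks: mean of 1 − 0.95^(3k+4) = 0.474.
- Completion if ever severe: 0.7 × 0.676 / (0.7 × 0.676 + 0.3 × 0.474) = 0.769.
- Completion if never severe: 0.7 × 0.324 / (0.7 × 0.324 + 0.3 × 0.526) = 0.590.

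That is 77% against 59%. At 2% weekly it is 79% against 66%, and at 10% it is 75% against 45%.

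**Step 3. OS and PFS under no true association, *ever severe* rule.** These are simulated cohorts of 134, with a Cox test from treatment start. Reports run to week 22 at most and follow-up is 24 months (104 weeks). All rates are assumed. Each cell shows the mean HR and the rejection rate at nominal 5%.

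| Assumed median | 2% weekly | 5% weekly | 10% weekly |
|---|---|---|---|
| OS 12 months (300 cohorts) | 0.76; 25% | 0.65; 58% | 0.42; 87% |
| OS 52 weeks, separate run (400) | 0.78; 19% | 0.67; 49% | 0.43; 83% |
| OS 80 weeks (800) | – | 0.70; 34% | – |
| PFS 26 weeks (800) | 0.71; 38% | 0.60; 80% | 0.40; 98% |
| PFS 35 weeks (800) | 0.74; 29% | 0.63; 68% | not reported (convergence failures) |
| PFS 52 weeks (800) | 0.78; 16% | 0.67; 48% | 0.48; 81% |

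**Step 4. Other severity rules.** These are again null cohorts of 134 (300 of them), with assumed median OS of 12 months, 70% completion, stable patient-level severity plus weekly noise, and a median split.

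| Rule | OS HR | Rejection | Completion, severe vs not |
|---|---|---|---|
| Peak score | 0.81 | 21% | 73% vs 67% |
| Mean weekly score | 1.00 | 4.7% | 70% vs 70% |
| Baseline score | 0.99 | 7% | 70% vs 70% |

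The 7% is compatible with 5% at 300 cohorts: the standard error is √(0.05 × 0.95 / 300) = 1.3 percentage points. A separate run gave HR 0.81 with 19% for the peak score and HR 0.99 with 4% for the mean.

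**Step 5. Ordering the data.** With the *ever severe* group fixed at a week-6 landmark and only later events counted, the null HR was 0.98–1.03 and the rejection rate 3–7% across the settings run.

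**Step 6. Problem (b).** No arithmetic was done. Weekly reporting continues through and beyond toxicity, complications and unplanned visits, and the Data analysis section does not restrict the category to earlier reports. Averaging does not help, because reports made after the event enter the mean.

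**The case against.** The strongest reply is that the Data analysis section states no severity rule at all. It does not say *ever severe*, does not say that reports made after an event will be used, and does not rule out a landmark or a time-varying score. A journal article may leave such details to an analysis plan that is not shown. The only score the article displays is a mean ± SD in the sample size section, which is closer to an average than to a peak, and under an average problem (a) disappears.

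Much of this stands. The hazard ratios in Step 3 belong to one hypothetical rule and are not a prediction for this study. That the category uses on-treatment reports at all is read from the Abstract and the Primary outcome section. A baseline-only category would avoid both problems, but it would not answer the trajectory question posed in the Abstract.

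The reply does not remove the point. The article fixes on-treatment exposure, concurrent outcomes, a time origin at treatment start and a significance test. These need an ordering rule to fit together. A mean score still leaves (b).

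Three stronger readings are tempting but unsupported:

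- **That the toxicity comparison is a tautology.** The overlap is partial. The exposure also covers 16 MDASI-LC symptoms and six functional items, and the outcome includes hepatic and endocrine toxicity, which the listed items do not measure directly.
- **That the analysis is unadjusted.** The article names no model and does not say so; a covariate list may exist elsewhere.
- **That the study commits to using symptoms as warning signals.** The Background raises that as an open question in the field. Most sections speak of association or correlation, although the Abstract does speak of consequence.

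**Conclusion.** The point holds as a matter of time order. As written, the plan lets the amount and timing of symptom data depend on the outcomes those data are compared with.

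The size of the length-of-observation bias cannot be fixed from the documents. Under the assumed event rates it runs from none (per-patient mean), through an OS hazard ratio of about 0.81 with about 20% false positives (median split on peak), to about 0.65–0.70 (range about 0.4–0.8) with completion of 77% against 59% (*ever severe*). Where it occurs, it favours the severe group. The reversed-order problem remains under every on-treatment rule considered, including the mean, and has not been quantified.

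The affected outcomes are secondary and exploratory.

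**What to change.** In the Data analysis section:

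1. Define severity from reports up to a fixed landmark, for example the mean weekly score in weeks 1–6. Relate it only to outcomes after the landmark, in patients still at risk of each outcome. Alternatively, enter the weekly score as a lagged time-varying covariate.
2. For toxicity, complications and unplanned visits, use only reports dated before onset.
3. Present irAE-item scores recorded at the same time as graded toxicity as agreement between patient and clinician assessment, not as prediction.
4. As a secondary improvement, adjust for the baseline symptom score, which is collected, and for whichever pre-treatment characteristics are actually recorded. The Data collection section mentions demographics and clinical characteristics without listing them.

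The cost is wording and code, with no new questionnaires. Onset dates of toxicity, complications and unplanned visits are needed; the article does not say that they are recorded, so this should be confirmed. Events before the landmark drop out of the landmark analysis, whereas the time-varying model keeps them.
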